### Data collection procedures

The study will include all women recruited from 1^st^ May 2022, up until the end of the delivery of the service (anticipated to be at the end of 2023).

Pregnant women complete a detailed questionnaire when recruited to BiBBS regarding their prenatal attachment, mental health, socio-demographics, family circumstances and more. Data provided from this questionnaire will enable intervention and control groups to be matched, where individual intervention participants can be matched to > 1 control group participant(s) (see statistical methods section for details).

All BiBBS mothers will complete outcome measures at 6–10 weeks after birth. The data are collected either by phone or at a physical home visit. The questionnaires include: the Patient Health Questionnaire-8 (PHQ-8), Generalised Anxiety Disorder assessment-7 (GAD-7), and the Mothers Object Relations Scale-Short Form (MORS-SF) (see below for details).

### Outcomes

#### Primary outcome measure (maternal sensitivity)

##### Mothers Object Relation Scale—Short Form (MORS-SF) 

To measure maternal sensitivity, we use the Mothers Object Relations Scales (MORS). The MORS is a validated measurement tool of the relationship between a caregiver and their infant or child. It measures a caregiver’s perception of their infants/child’s thoughts, feelings, and intentions towards them. It assesses mothers’ models of their infants on two axes; the emotional warmth-coldness and the invasion-withdrawal of the infant towards the mother [39]. As the original scale has 44 items, we choose the ‘short-form’ of this measure with 14 items to reduce participant burden (MORS-SF). The MORS-SF has been found to have good psychometric properties in Hungarian and British samples, with associations to maternal depression and infant temperament [39].

#### Secondary outcomes measures (maternal mental health)

##### Patient Health Questionnaire (PHQ-8) and Generalised Anxiety Disorder Assessment (GAD-7) questionnaires

The PHQ-9 and GAD-7 are widely used tools to assess depression and anxiety, respectively [33, 47]. They have previously been used as outcome measures in parenting programme trials [8]. The PHQ-9 has been found to successfully differentiate between depressed and non-depressed mothers, supporting its use to screen for postpartum depression [26].

BiBBS uses the PHQ-8, which is also a widely used tool to assess depression and only differs to the PHQ-9 in that it omits Item 9 [34]. Item 9 of the Patient Health Questionnaire-9 (PHQ-9) queries about thoughts of death and self-harm. Validation studies have found that both the PHQ-9 and PHQ-8 have similar diagnostic properties [44, 54]. To compare the PHQ-8 outcomes, any participants with a PHQ-9 questionnaire will have data dropped for Item 9.

#### Birth outcomes

Data will be linked to routinely collected birth outcomes by maternity services and Health Visitors for both the intervention and the control group. We will look at descriptive differences across delivery method, gestation period, and baby weight. In the case of multiple births (e.g. twins) we will use only the first-born child’s data.

#### Proxy indicator for poor perinatal mental health

BiBBS has developed a proxy indicator for the identification of poor perinatal mental health which uses predetermined code lists to identify any indication of poor maternal mental health in maternity electronic healthcare records, health visitor and GP records throughout pregnancy and up to one year after birth. Indicators include positive perinatal mental health screening, or use of assessment tools such as PHQ-9/GAD-7, referrals to perinatal mental health services and relevant prescriptions. Coded data will be examined for indication of perinatal mental health, with reference to predetermined code lists. More information will be available in the statistical analysis plan.

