### Objectives

The current study will examine the causal effectiveness of the Baby Steps intervention in a real-world setting, within a socioeconomically deprived and ethnically diverse area in Bradford. Baby Steps is commissioned by Better Start Bradford and delivered by Action for Children. The authors of this study are independent of the delivery or design of the service.

This study will use a matched-control comparison group. The specific aims of this study are to (1) assess whether the universally and remotely delivered Baby Steps programme is effective in improving the primary outcome of postnatal maternal sensitivity and (2) the secondary outcome of postnatal maternal mental health when compared to services as usual at 6–10 weeks postnatal. This study also aims to (3) assess whether the effects of Baby Steps on postnatal maternal sensitivity are mediated by postnatal maternal mental health.

This study has additional objectives with outcomes nested in routinely linked data, however, it will be underpowered to ascertain causal effectiveness in these outcomes. We aim to (4) assess differences in birth outcomes (delivery type, weight, gestation, feeding) and (5) assess differences in the identification and prevalence of poor perinatal mental ill health inferred through routine data linkage across the two groups. Finally, the economic analysis of this study will (6) estimate the cost of the intervention (including delivery and training to deliver Baby Steps) and (7) assess the feasibility of collecting health related resource use data for a future full economic evaluation.

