### Intervention

Baby Steps is a ‘relationship-based’ antenatal parent education programme developed by the NSPCC (https://learning.nspcc.org.uk/services-children-families/baby-steps).

Baby Steps delivery begins around the 26th to the 30th week of pregnancy. The programme under evaluation differs to the original programme in that it is delivered to groups remotely but retains some face-to-face contact. To adapt to remote delivery, the service delivery team have condensed the intended nine individual sessions into six group sessions. There are two one-to-one initial sessions (one of which is in the participant's home, one of which is virtual) prior to the course commencing to help build relationships between families and practitioners. Then there are four online, remote, group sessions before the baby is born. After the baby is born there is another in person home visit, followed by two online group sessions. See Table 1 for an overview of the sessions and timings.

**Table 1 Tab1:** Overview of programme content and timings

Content	Time of delivery

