#### Descriptive data

As birth outcomes and the proxy poor perinatal mental health outcomes are categorical, the required sample sizes for detecting differences in these outcomes is very large and unlikely to be obtained within this evaluation. We therefore do not expect to be able to assess effectiveness in these outcomes, but will report descriptive trends in birth outcomes, and in poor perinatal mental health for the intervention and control groups in our analysis.

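### The proxy for poor perinatal mental health counts codes from before Baby Steps starts, and the reason given for not assessing birth outcomes does not fit gestation and birth weight

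*Protocol article*

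**What the plan says.** **Proxy indicator.** The section on the proxy describes a cohort-wide BiBBS indicator that uses code lists "to identify any indication of poor maternal mental health in maternity electronic healthcare records" and in "health visitor and GP records throughout pregnancy and up to one year after birth". Qualifying codes include positive screens, referrals, prescriptions, "or use of assessment tools such as PHQ-9/GAD-7". The section closes with "More information will be available in the statistical analysis plan". Objective 5 is to "assess differences in the identification and prevalence of poor perinatal mental ill health inferred through routine data linkage across the two groups".

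**Programme start.** The Intervention section states: "Baby Steps delivery begins around the 26th to the 30th week of pregnancy".

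**Birth outcomes.** Objective 4 names delivery type, weight, gestation and feeding. The Birth outcomes section plans "descriptive differences across delivery method, gestation period, and baby weight". The abstract lists low birth weight where the Methods list baby weight.

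**Reason for description only.** The Descriptive data section begins "As birth outcomes and the proxy poor perinatal mental health outcomes are categorical, the required sample sizes" and goes on to say that the sample needed is too large to be reached, so effectiveness will not be assessed and trends will be described. The Objectives section also declares objectives 4 and 5 underpowered for causal effectiveness.

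**The concern.** An outcome should be able to change after exposure. Under an any-code rule, a woman coded at 12 weeks is positive whatever Baby Steps later does. Counting such women has two effects. It shrinks any real difference, because they are fixed as positive in both groups. It also lets a group difference in earlier mental health, if one remains after matching, appear in a table that readers will take as an outcome comparison.

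The birth-outcome point is separate. The protocol infers from categorical outcomes that a very large sample is needed, and from that that only trends can be shown. For delivery method and for the proxy this reasoning is sound. For gestation and birth weight kept as measurements it is not, because a continuous outcome follows the same sample-size arithmetic as the MORS-SF. What is at stake is an interval estimate for two outcomes, and a correct explanation of why these results are exploratory.

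**Working it through.** **1. The plan's own sample size.** Inputs from the Sample size calculations section: two-sample t-test, two-sided alpha 5%, power 80%, difference 2.35, SD 4.7.

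- d = 2.35 / 4.7 = 0.50.
- The t-test needs 63.8, so 64 per group (128 in total; 130 stated).
- Power: 80.8% at 65:65, 82.1% at 56:84, 81.8% at 50:100, 82.4% at 45:135.

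The stated figure reproduces. No figure is given for the birth outcomes or the proxy.

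**2. How much of the window precedes the programme.** Assume a 40-week pregnancy and a 52-week postnatal year, so a 92-week window.

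- Share of pregnancy: 26/40 = 65% to 30/40 = 75%.
- Share of the whole window: 26/92 = 28% to 30/92 = 33%.

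These are shares of calendar time. They are not shares of codes or of women, and they do not measure bias.

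**3. Dilution, by illustration.** Let q be the proportion with a code before the start, equal in both groups, and p the probability of a later code, taken as the same whether or not there was an earlier one. Then

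P(any code) = q + (1 − q)p, and the risk difference for any code = (1 − q) × the risk difference for later codes.

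Assume later codes in 20% of controls and 10% of intervention mothers (difference 10 points, ratio 0.50). All these rates are assumptions.

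| q | Control | Intervention | Difference (points) | Ratio |
|---|---|---|---|---|
| 10% | 28.0% | 19.0% | 9.0 | 0.68 |
| 20% | 36.0% | 28.0% | 8.0 | 0.78 |
| 30% | 44.0% | 37.0% | 7.0 | 0.84 |
| 46% | 56.8% | 51.4% | 5.4 | 0.90 |

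The 46% is the share of pregnant BiBBS women reporting mild to severe depressive symptoms (Study setting). It is used only as a high value, since symptoms on a questionnaire are not coded records.

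**4. Carry-over of imbalance, by illustration.** Suppose the programme has no effect, later codes occur in 20% of both groups, and earlier codes in 40% of one group and 30% of the other.

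- 0.40 + 0.60 × 0.20 = 52%.
- 0.30 + 0.70 × 0.20 = 44%.

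An 8-point difference appears with no effect. The 40% and 30% are assumed and take no account of matching, which should make such a gap smaller.

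**5. Gestation and birth weight as continuous outcomes.** At an assumed 0.5 SD, the requirement is the same 64 per group as for the MORS-SF. The smallest effect detectable with 80% power is 0.495 SD at 65:65, 0.485 SD at 45:135 and 0.41 SD at 62:187. Ignoring any effect of matching on the variance, the half-width of a 95% interval at 65:65 is about 1.96 × √(1/65 + 1/65) = 0.34 SD.

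**6. The same shift after dichotomising.** With control rate p1 and a normal outcome shifted by 0.5 SD, p2 = Φ(Φ⁻¹(p1) − 0.5). Assumed control rates of 6% and 12% give 2.0% and 4.7%. The two-proportion formula (normal approximation, pooled variance under the null) then needs 375 and 225 per group, with power at 65:65 of 21% and 32%. So the very large sample is a consequence of cutting the measurement into two classes, not of the measurement itself.

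**The case against.** Several counter-arguments have force.

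- **The SAP may restrict the window.** The article defers detail to it, and how individual codes are scored is rightly left there. The window itself, however, is already stated and covers the whole of pregnancy. A promise of more information does not undo it.
- **Matching covers prenatal mental health.** PHQ-8 and GAD-7 scores are matching variables, collected mostly at 24 to 28 weeks, close to programme start. This should limit imbalance in earlier codes. It does nothing about dilution, which arises even with perfect balance.
- **Both objectives are descriptive and declared underpowered.** This stands. There is no test, threshold or decision rule. A reader might infer that the conclusions on objectives 4 and 5 are invalid, or that estimates for birth outcomes are forbidden. The documents do not support either reading: what is set aside is an effectiveness claim, and group differences will still be described.
- **Low birth weight is categorical.** If the abstract gives the intended form, the stated reason is right for weight. The article then contradicts itself on form, and gestation period is still listed as a measured quantity in both places.
- **0.5 SD is borrowed.** It was chosen for the MORS-SF for want of a minimum important difference. The Background cites a meta-analysis that found no evidence of improved foetal birth outcomes from antenatal programmes. A realistic effect may be well below 0.5 SD, so underpowered may still be the right word, for a different reason.

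A further tempting inference is that programme contact inflates the proxy in intervention mothers, because use of a PHQ-9 or GAD-7 counts, midwives or health visitors co-facilitate sessions, and there are questionnaire visits. No passage says that those questionnaires include these tools or enter the linked records, and objective 5 covers identification as well as prevalence. This is possible but not shown.

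**Conclusion.** The point holds in two limited parts.

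First, as written, the objective 5 comparison counts codes from before exposure. The direction of one consequence is clear: a true difference is diluted. Residual baseline imbalance can also enter, in either direction. The size of either cannot be derived from the documents. The drop from 10 points to between 9 and 5.4 rests wholly on assumed rates, and the 28–33% should not be quoted as a measure of bias.

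Second, the reason in the Descriptive data section is wrong for gestation and birth weight as the Objectives and Birth outcomes sections list them, and the abstract is inconsistent with those sections on the form of weight. At an assumed 0.5 SD these outcomes have about 81% power at 65:65. This does not show that the study is adequately powered for them, since no document supports that effect size.

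The primary outcome and the main mental health scales are unaffected. Both parts are cheap to put right before the linked data are analysed.

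**What to change.** 1. **Proxy window.** For the group comparison, count only codes dated after the first Baby Steps contact. Give each control the gestation at which her matched intervention mother had that contact. Report earlier codes as a baseline characteristic by group. The whole-pregnancy indicator can still be shown as the cohort's standard definition, labelled as such. Cost: a date filter on linked records and an index date for each control, with no new data. The downside is fewer events and so less precise proportions.
2. **Birth outcomes.** State whether weight is analysed as measured, as low birth weight, or both, and align the abstract, Objectives, Birth outcomes and Descriptive data sections. Limit the categorical argument to the outcomes that are categorical.
3. **Estimates.** Report gestation and birth weight as exploratory mean differences with 95% confidence intervals from the matched regression. The planned covariate for child age in days is not needed for outcomes fixed at birth. Do not claim 80% power other than for an assumed 0.5 SD effect. Cost: two extra regressions.
4. **Optional.** Show codes for use of an assessment tool separately from positive screens, referrals and prescriptions, so that identification and prevalence can be read apart.

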## Background

The perinatal period refers to both pregnancy (the antenatal period) and the first 12 months after childbirth (the postnatal period) [37]. We use the terms ‘women’ and ‘maternal’ to refer to birthing parents, we recognise however that not all birthing parents are women. Perinatal mental health problems carry an estimated long-term cost to society of £6.6 billion for each 1-year cohort of births, with most of this cost relating to negative impacts on the child rather than the mother [4]. Perinatal mental health problems can have an adverse effect on maternal perceptions of infant temperament and mother–child bonding [18, 35], and on the cognitive, behavioural, and psychomotor development of their child [31, 36]. Improving perinatal mental health is therefore crucial for improving mother–child bonding, to foster the development of children’s attachment, social and emotional competence, cognitive functioning, physical health, and mental health [19, 36, 42].

Specifically within the postnatal period, postnatal depression affects an estimated 10–19% of women globally [29]. In the UK, 11% of women have a diagnoses or symptoms of postnatal depression, with increased risk for those living in the most deprived areas [55]. A systematic review revealed that women belonging to ethnic minority groups are at an increased risk of reduced identification and management of poor mental health in the perinatal period [41].

Parenting programmes are those which help parents and their children to develop positive behaviours and relationships [24]. Early parenting programmes that reduce parental psychological distress and improve parent–child relationships during the perinatal period have the potential to reduce the economic burden on society and improve outcomes for children [1, 2]. However, systematic reviews which have synthesised evidence about these interventions have shown mixed results depending on the outcome examined.

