**Fig. 1 Fig1:**
[figure not shown]
Directed Acyclic Graph of associations between confounders, treatment exposure, and primary outcome

Table 2 describes the covariates that we will use for propensity score matching obtained from the BiBBS baseline questionnaire completed before the child is born. All matching variables are at the level of the mother, not the child. Variables were selected to be matched upon if they were thought to have an association with both uptake of treatment, and with the outcomes (maternal sensitivity, maternal mental health), and there was empirical evidence to suggest this was the case (see references in Table 2).

**Table 2 Tab2:** Covariates for matching obtained from BiBBS baseline questionnaire

Covariates (measurement tool if relevant)	Measurement	Justification
Prenatal attachment (Prenatal Attachment Inventory)	Continuous	[13]
Prenatal Depression (PHQ-8)	Continuous	[13]
Prenatal Anxiety (GAD-7)	Continuous	[13]
Ethnicity	Categorical	[13, 41, 51]
Socioeconomic position (financial security)	Continuous	[28, 48, 51]
Mother age	Continuous	[13, 28]
Parity (first child or not)	Continuous	[48]
Speaks English	Binary	[11, 51]

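### The routine-data mental-health indicator counts codes from before Baby Steps starts, so the descriptive group comparison in objective 5 mixes pre-exposure events with possible programme effects

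*Protocol article*

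**What the plan says.** In the protocol article, Outcomes, the section on the proxy indicator describes a search of coded data for any sign of poor maternal mental health: positive screens, use of assessment tools, referrals and relevant prescriptions. The sources are maternity records and "health visitor and GP records throughout pregnancy and up to one year after birth". This matches the definition in Background: "The perinatal period refers to both pregnancy (the antenatal period) and the first 12 months after childbirth".

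The Intervention section puts the start of exposure much later than the start of that window: "Baby Steps delivery begins around the 26th to the 30th week of pregnancy".

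Objective 5 is to "assess differences in the identification and prevalence of poor perinatal mental ill health inferred through routine data linkage across the two groups". The Abstract lists the same indicator among the secondary outcomes. Two statements limit its role. Objectives says of the routine-data outcomes that "it will be underpowered to ascertain causal effectiveness in these outcomes", and Descriptive data says the authors "will report descriptive trends in birth outcomes, and in poor perinatal mental health for the intervention and control groups in our analysis". The section on the indicator closes with a pointer: "More information will be available in the statistical analysis plan".

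Table 2 ("Covariates for matching obtained from BiBBS baseline questionnaire") lists prenatal attachment, PHQ-8, GAD-7, ethnicity, financial security, age, parity and English. It does not list earlier routine mental-health codes. No section splits the indicator's window at programme start or makes allowance for women already coded by then.

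**The concern.** A code recorded before the programme starts cannot be a result of it. Because any single code makes the indicator positive, a woman coded in early pregnancy stays positive whatever happens later. The two group percentages in objective 5 therefore combine what the groups were like before exposure with what happened afterwards.

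There are two consequences. If earlier coding is equally common in both groups, it dilutes any difference that arises after programme start. If it is not, the difference in earlier coding enters the comparison directly and can look like an effect or hide one. Groups are formed by uptake rather than randomisation, so equality cannot be taken for granted. What is at stake is how readers interpret one descriptive table, which will show the intervention and control figures side by side.

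**Working it through.** The article states no rate, effect size or power for this indicator, so there is no figure of its own to reproduce.

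**1. How much of the window precedes exposure.** Inputs: start at 26 to 30 weeks (Intervention); window from the start of pregnancy to 52 weeks after birth (proxy indicator section); pregnancy length of 40 weeks (assumed, range 37 to 42).

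- Share of the whole window: 26/(40+52) = 28.3% to 30/(40+52) = 32.6%. Over 37–42 weeks: 26/94 = 27.7% to 30/89 = 33.7%.
- Share of the antenatal part: 26/40 = 65% to 30/40 = 75%. Over 37–42 weeks: 26/42 = 62% to 30/37 = 81%.

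These are shares of calendar time. The share of coded events is not given and may differ.

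**2. Equal earlier coding: dilution.** Let *pre* be the proportion already coded at programme start and *post* the risk of a first code afterwards among women not yet coded. Then

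P(ever coded) = pre + (1 − pre) × post, so difference in ever coded = (1 − pre) × difference in post.

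Assume post = 30% in controls and 20% in the intervention group, a difference of −10.0 points and a risk ratio of 0.67.

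| Already coded, both groups | Control | Intervention | Difference (points) | Risk ratio |
|---|---|---|---|---|
| 10% | 37.0% | 28.0% | −9.0 | 0.76 |
| 20% | 44.0% | 36.0% | −8.0 | 0.82 |
| 30% | 51.0% | 44.0% | −7.0 | 0.86 |
| 46% | 62.2% | 56.8% | −5.4 | 0.91 |

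All the rates are assumptions. The 46% row borrows the cohort's questionnaire figure for depressive symptoms in pregnancy (Study setting), which is not a rate of coded records.

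**3. Unequal earlier coding: distortion.** Same post-start risks, 20% of controls already coded (control total 44%).

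- Intervention 30% already coded: 0.30 + 0.70 × 0.20 = 44%. The 10-point difference disappears.
- Intervention 35% already coded: 0.35 + 0.65 × 0.20 = 48%. The sign reverses, by 4 points.
- No effect at all (post = 30% in both), 30% v 20% already coded: 0.30 + 0.70 × 0.30 = 51% against 0.20 + 0.80 × 0.30 = 44%. A 7-point difference appears from nothing.

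**4. Could such a gap arise?** Treating the groups as independent samples, the chance standard error of the difference in earlier coding is √[p(1 − p)(1/n₁ + 1/n₂)]. Group sizes come from the Sample size section.

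- 62:187: 5.9 points at p = 20%, 6.7 at p = 30%.
- 45:135: 6.9 points at p = 20%, 7.9 at p = 30%.

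A 10-point gap is thus about 10/7.9 = 1.3 to 10/5.9 = 1.7 standard errors. That is before matching, which should narrow it by an unknown amount.

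**The case against.** The strongest reply is that nothing inferential rests on this. The outcome is declared underpowered and will only be described; the window is the ordinary meaning of perinatal; and the analysis plan, not shown here, is to say more. Matching uses PHQ-8 and GAD-7 from a questionnaire taken mostly at 24–28 weeks, close to programme start. The offer is now universal, so referral on mental-health need is not the stated process.

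Much of this stands. Descriptive status confines the consequence to one table, matching makes an imbalance less likely, and a whole-perinatal window is reasonable for describing prevalence. Three things remain:

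- The power caveat concerns precision, whereas counting pre-exposure codes is a bias that a larger sample would not remove.
- The window is stated in the article rather than left open, and it does not suit a comparison of groups formed late in pregnancy. The analysis plan may refine it, but the article does not say so.
- Symptom scores are not codes. A woman with a prescription or referral in early pregnancy may score low at baseline. Matching also does nothing about dilution.

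A reader might infer more: that the comparison will be reversed, that about a third of counted events precede exposure, or that the study's effectiveness conclusions are compromised. The documents support none of these. Reversal needs an imbalance that no document shows; the third is time, not events; and the effectiveness outcomes are questionnaires completed at 6–10 weeks after birth.

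**Conclusion.** The point holds in a limited form. Followed as written, the indicator counts pre-exposure codes as outcome in the objective 5 comparison. The dilution factor of one minus the proportion already coded is exact when earlier coding is equal in the two groups; its value is unknown because no routine-code rates are given. Distortion requires unequal earlier coding, which the matching reduces but does not rule out, and reversal is the less likely outcome. The 30% v 20% risks and all earlier-coding rates above are illustrative assumptions. The primary outcome (MORS-SF) and the PHQ-8 and GAD-7 outcomes are not affected. It is worth correcting because the result will be shown by group and the correction is cheap.

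**What to change.** In the proxy indicator section, and correspondingly in the analysis plan:

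- Define an index date: the initial home visit for intervention mothers, which is already the entry point for the intention-to-treat analysis, and for each matched control the date she reached the same gestation.
- Report codes between the start of pregnancy and the index date by group, as a baseline characteristic.
- For objective 5, report codes after the index date in two ways: first post-index codes among women with no earlier code in that pregnancy, and post-index codes in all women with adjustment for, or stratification by, earlier coding.

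Both are needed. Simply counting every post-index code would still pick up continuing prescriptions and referrals in women already coded, and so carry an earlier imbalance forward. The arithmetic above applies to women not coded before.

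Whole-perinatal prevalence can still be shown, labelled as a description rather than a comparison of outcomes.

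The cost is one definition and dated codes and gestation in the linked extract. The downside is fewer counted events and less precision in an outcome already declared descriptive.
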